## Abstract

**Background:**

Palliative care should be provided according to the individual needs of the patient, caregiver and family, so that the type and level of care provided, as well as the setting in which it is delivered, are dependent on the complexity and severity of individual needs, rather than prognosis or diagnosis [1]. This paper presents a study designed to assess the feasibility and efficacy of an intervention to assist in the allocation of palliative care resources according to need, within the context of a population of people with advanced cancer.

**Methods/design:**

People with advanced cancer and their caregivers completed bi-monthly telephone interviews over a period of up to 18 months to assess unmet needs, anxiety and depression, quality of life, satisfaction with care and service utilisation. The intervention, introduced after at least two baseline phone interviews, involved a) training medical, nursing and allied health professionals at each recruitment site on the use of the *Palliative Care Needs Assessment Guidelines *and the Needs Assessment Tool: Progressive Disease - Cancer (NAT: PD-C); b) health professionals completing the NAT: PD-C with participating patients approximately monthly for the rest of the study period. Changes in outcomes will be compared pre-and post-intervention.

**Discussion:**

The study will determine whether the routine, systematic and regular use of the *Guidelines *and NAT: PD-C in a range of clinical settings is a feasible and effective strategy for facilitating the timely provision of needs based care.

**Trials registration:**

ISRCTN21699701

## Background

The delivery of appropriate and equitable care is a challenge facing many areas of health care, including palliative care. In fact, the health care experiences of people with life limiting illnesses have become a primary concern in recent years, with literature suggesting that the management of advanced cancer is lacking in terms of access [2]. Despite the increased attention, issues surrounding when and how palliative care should be delivered, as well as who should receive this care are yet to be resolved.

Palliative care has relied in part on prognosis or diagnosis based models to guide delivery of care. However, the need to provide palliative care in a more accessible and equitable manner has led to Palliative Care Australia (PCA) recommending a more needs-based model [1]. This model offers a way to improve the delivery of palliative care by triaging people with life limiting illnesses such as cancer according to complexity of their needs. Providing care on the basis of needs offers a way to ensure that the finite specialist palliative care resources available are provided to those people who need them most [3], while allowing less complex needs to continue to be met by primary care or allied health services. Hence, patients with minimal needs can continue to be cared for by their primary care team; while those with intermediate or complex needs may require the consultative or continued involvement of specialist providers [1].

However, implementing a needs based model has its own challenges, including how to define need and how and when to assess need [4]. Having best practice standards and pathways to referral may assist with identifying those who require the assistance of palliative care services and also those who no longer require specialist palliative care input [5]. The *Palliative Care Needs Assessment Guidelines*[6] (hereafter referred to as the *Guidelines*) were developed in an attempt to fill a gap nationally and internationally[6] by educating and informing health professionals about the issues that affect people with advanced cancer, their families and professional carers to facilitate timely referral to specialist palliative care services if required. As ensuring optimal compliance with guidelines is a primary concern for developers [7-11]; the *Needs Assessment Tool: Progressive Disease - Cancer (NAT: PD-C) *was developed to complement the *Guidelines*[6].

The NAT: PD-C was designed for ongoing use in both generalist and specialist care settings. Rather than simply determining who would benefit from a referral to a specialist palliative care service, the NAT: PD-C assists health professionals in matching the types and levels of need with the most appropriate person or service to address that need [12]. Psychometric properties of the NAT: PD-C were initially explored in a pilot study with simulated patients and caregivers [under its original name of the *Palliative Care Needs Assessment Tool*][12]. Further testing in a clinical palliative care setting confirmed the NAT: PD-C as a highly acceptable and efficient tool that can be used by health professionals with a range of clinical expertise [13]. However, the need for further evaluation of the *Guidelines *and NAT: PD-C to assess patients and their caregivers at multiple time points and determine the responsiveness of the NAT: PD-C to change over time has been acknowledged. In response to this, the research team undertook the following prospective, multi-site, multi-discipline longitudinal study.

The aims of the study were two-fold: to assess the impact of the systematic and ongoing use of the *Guidelines *and NAT: PD-C on patient and caregiver outcomes including level of need, quality of life, anxiety and depression and satisfaction with care; and to assess their impact on patient service use and referral patterns.

## Methods/design

### Ethical approval

The study was approved by the Human Research Ethics Committees of the University of Newcastle and of the Area Health Services of Hunter New England, Sydney South West, South Eastern Sydney and Illawarra.

### Study design

The study utilises an interrupted time series design [14], with data collected at multiple time points before and after the intervention is introduced [15]. By collecting data before and after the intervention, researchers can determine whether the intervention has an effect significantly greater than the underlying secular trend [15,16]. One advantage of this design is that it allows both the short-term and long-term effects of the intervention to be examined more akin to an effectiveness study than a more limited efficacy study [14]. Moreover, this design is highly suited for use in smaller populations and complex interventions [14].

### Participants

Inclusion criteria for patients are: (1) having a diagnosis of advanced cancer, ie, no longer amenable to cure, with either extensive local or regional spread, or metastatic disease; (2) being aged 18 years or older; (3) understanding English sufficiently well to complete questionnaires and telephone interviews; and (4) judged by the clinic staff as emotionally and cognitively capable of participating. Caregiver inclusion criteria are: (1) being nominated by the patient as the primary carer or family member who has provided, or may provide when needed, the most help to the patient; and (2) understanding English sufficiently well to complete questionnaires and telephone interviews.

## Sample size

The main outcome of interest in this study is each patient's level of unmet needs as measured by the Supportive Care Needs Survey - Short Form (SCNS-SF34) [17]. The percentage of people reporting at least one moderate or high need in each of the domains in the SCNS was calculated pre- and post-intervention. Having a moderate or high need was chosen as the category indicating a need as it has been suggested that "by evaluating psychosocial interventions with patients experiencing moderate to severe symptoms, future research is likely to yield findings of greater relevance to clinical practice" [18]. A systematic review of unmet supportive care needs in people with cancer reported that a number of studies have used a classification of moderate or high need to assess the prevalence of needs in people with cancer [19]. Many of these studies have reported prevalence for individual items (range 2-48%) rather than the prevalence of people with at least one need in each domain [20-23]. A recent study reported that the percentage of people with cancer identified as having at least one moderate or high need for help using the of the SCNS-SF34 ranged from 15% (sexuality domain) to 53% (psychological domain) [17]. Six spiritual items from the Needs Assessment for Advanced Cancer Patients (NA-ACP) [24]; a 132 item instrument assessing the needs of people with advanced incurable cancer [24], were assessed using the same response options as the SCNS.

Assuming a maximum prevalence of 50% (worst case scenario) at pre-intervention for all domains, it was calculated that using a 5% significance level and having a minimum of 407 patients would give the study 80% power to detect a reduction in prevalence of 10% in each of the five SCNS-SF34 domains and one NA-ACP domain post-intervention. However, this estimation of expected change in prevalence could not be supported by any previous literature, as few studies have looked at changes in needs over time or changes in the prevalence of needs resulting from an intervention [19].

Caregivers of all consenting patients will also be invited to participate in the study. Of an estimated 407 patients consenting to participate, it is anticipated that 60% will have a consenting caregiver (n = 245).

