#### Changes in primary and secondary outcomes over time

For each patient, level of need, anxiety, depression and quality of life will be measured repeatedly during the study and therefore a Generalised Estimating Equation (GEE) model will be used to analyse the data [39]. In this study the GEE model will fit time as a factor and also analyse the number of CATIs completed as an interaction variable. Age, gender, time since diagnosis, co-morbidity score and presence of a caregiver will be included as potential confounding variables for patient participants. Age and gender will also be included as confounder for caregiver participants. For the purpose of this study, presence of a caregiver will include patients who had a participating caregiver at first assessment as well as patients who subsequently indicated they had a caregiver in any of their CATIs (irrespective of whether their caregiver consented to participate). GEEs will be run for both continuous and categorical outcome variables adjusting for the potential confounders listed above to ascertain whether the intervention had any impact on patient and caregiver outcomes.

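### The 80% power quoted for 407 patients matches a two-independent-samples calculation, not the single repeatedly interviewed cohort this study follows, and the direction of the error is undetermined

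*Protocol article*

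**What the plan says.** All places are in the protocol article.

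- **Sample size.** The calculation starts from "Assuming a maximum prevalence of 50% (worst case scenario) at pre-intervention for all domains" and "using a 5% significance level", and states that "having a minimum of 407 patients would give the study 80% power to detect a reduction in prevalence of 10" per cent, for each of six needs domains (five from the SCNS-SF34, one from the NA-ACP). The caregiver estimate then begins "Of an estimated 407 patients consenting to participate", so the same 407 is both the number required and the number expected to enrol.
- **Study design.** An interrupted time series, with "data collected at multiple time points before and after the intervention is introduced", intended to show an effect beyond the underlying secular trend.
- **Abstract (Methods/design) and Materials.** Interviews every two months for up to 18 months; the intervention starts after two or more baseline interviews.
- **Changes in primary and secondary outcomes over time.** Outcomes are "measured repeatedly during the study and therefore a Generalised Estimating Equation (GEE) model will be used", with time as a factor.
- **Participants.** Patients have advanced cancer that can no longer be cured.

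The sample-size text mentions no within-patient correlation, number of interviews, trend adjustment or loss to follow-up.

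**The concern.** A power figure describes a particular comparison under a particular design. The 407 appears to come from comparing one group of 407 people with a second, different group of 407. This study has no second group: the same patients supply the before and after data.

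Three features of the actual design are left out, and they do not all act in one direction. Positive within-patient correlation makes a before/after contrast more precise than the independent-samples formula assumes. Patients who die or withdraw before any post-intervention interview make it less precise. Separating the effect from a time trend also costs precision, by an amount that depends on the model.

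Unmet need is the study's main outcome. A null result would be read against an 80% that was not calculated for this study.

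**Working it through.** **1. Reproducing 407.** Inputs from the Sample size section: p1 = 0.50, p2 = 0.40, 5% significance, 80% power. Sidedness is not stated; two-sided is assumed.

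Two independent proportions, per group:

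n = [1.96·√(2·0.45·0.55) + 0.8416·√(0.25 + 0.24)]² / 0.10² = (1.379 + 0.589)² / 0.01 = 387.3

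With continuity correction:

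n′ = (387.3/4)·[1 + √(1 + 4/(387.3·0.10))]² = 407.1 **per group**

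Other standard calculations do not give 407:

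| Calculation | n |
|---|---|
| Two-sided, uncorrected | 388 |
| Unpooled variance | 385 |
| Arcsine | 388 |
| One-sided, uncorrected / corrected | 305 / 325 |
| One-sample | 194 |
| Paired (McNemar), zero correlation | 391 pairs |
| 10% *relative* fall (50% to 45%), uncorrected / corrected | 1565 / 1605 per group |

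The match therefore also shows that the target is 10 percentage points.

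**2. A simple paired before/after comparison.** The documents give neither a within-patient correlation (φ) nor a loss rate, so both are assumed.

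Discordance: ψ = p1 + p2 − 2·[p1·p2 + φ·√(p1(1−p1)p2(1−p2))]

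Power: Φ{[0.10·√m − 1.96·√ψ] / √(ψ − 0.01)}, where m is the number of complete pairs.

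| φ | ψ | Pairs for 80% | m = 407 (no loss) | m = 325.6 (20% loss) | m = 244.2 (40% loss) |
|---|---|---|---|---|---|
| 0 | 0.500 | 391 | 82% | 73% | 60% |
| 0.2 | 0.402 | 314 | 89% | 82% | 70% |
| 0.3 | 0.353 | 275 | 93% | 86% | 75% |
| 0.5 | 0.255 | 198 | 98% | 95% | 88% |

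The loss at which power falls to 80% is about 4% at φ = 0 (1 − 390.1/407), 32% at φ = 0.3 (1 − 274.7/407) and 51% at φ = 0.5 (1 − 197.8/407).

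**3. An effect separated from the trend.** Assumed: 407 enrolled, up to 9 interviews (18 months at two-month spacing), 10-15% of those remaining lost after each interview, variance 0.45·0.55 = 0.2475, exchangeable correlation 0.3. Power = Φ(0.10/SE − 1.96), with SE from generalised least squares. Where baseline counts vary, an equal mix of two, three and four is assumed.

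| Model for time | Baseline interviews | SE of step | Power |
|---|---|---|---|
| Linear trend + step | 2 | 0.028-0.030 | 91-95% |
| Categorical time + step | 2 to 4 | 0.038-0.042 | 67-74% |
| Linear trend + step + slope change | 2 to 4 | 0.034-0.037 | 78-84% |
| Linear trend + step + slope change | exactly 2 | 0.051-0.053 | 47-50% |

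At correlation 0.5, categorical time plus step gives 80-86%.

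**The case against.** The strongest reply is that 407 may well be conservative. For the before/after prevalence comparison that the Sample size section describes, ignoring positive correlation overstates the number needed, and GEE uses every available interview. This stands: with no loss, paired power is 82% or more at every correlation shown. It shows that the error may be harmless or favourable, not that 80% was derived for this design.

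Second, the formula is inferred. The article names neither formula nor sidedness, and 407.09 would conventionally be rounded up to 408. That is fair, and the match should be called an inference. No other variant tried comes as close.

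Third, a journal article leaves detail to the full protocol. The missing correlation or attrition workings would not be a finding alone. The point here is a firm number that the article does state and that does not fit the design it describes.

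A reader might infer more than the documents support:

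- *The trial is underpowered, or needs 2 × 407 = 814 patients.* A paired comparison needs at most 391 complete pairs on the figures above, so this does not follow.
- *Power is below 50%.* The 47-50% needs a slope-change term and exactly two baselines. The article specifies no slope-change term, and two is its minimum number of baseline interviews. Dropping only that term gives 91-95%.
- *Attrition cuts power to 75%, 67% or 54%* (20%, 40% or 60% never reaching a post-intervention interview). Those figures come from the independent-groups formula, which is the one that does not fit this cohort.

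**Conclusion.** The point holds in limited form. The stated 80% is not a property of a single cohort of about 407 patients, measured repeatedly and analysed by GEE, and it leaves no room for loss, because the required and consenting numbers are the same.

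The direction of the error is undetermined. Across the assumed correlations (0 to 0.5) and losses (0 to 40%), paired power runs from 60% to 98%. With trend adjustment at correlation 0.3, the answer moves from well above 80% to below it according to how time is modelled and how many baseline interviews patients give.

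Two parts need no assumed correlation or loss rate: the mismatch between the reconstructed calculation and the design, which rests on the inferred formula, and the equality of required and consenting numbers, which is in the text. The size rests wholly on assumptions that the documents neither support nor exclude. This should be corrected, but it does not show that the study is too small.

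**What to change.** Keep enrolment unchanged and restate the sample-size paragraph for the pre/post intervention term of the planned repeated-measures GEE. Give:

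- the number enrolled, and separately the number expected to have at least one post-intervention interview;
- the assumed within-patient correlation;
- the number of interviews before and after the intervention;
- how time enters the model used for the power calculation;
- the resulting power, or detectable difference, over a range of correlation and loss;
- the formula or method and the sidedness of the test;
- the target written as 10 percentage points (50% to 40%).

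The cost is a short recalculation and a rewritten paragraph, with no change to data collection. The downside is that the stated power may look less favourable under low correlation or high loss.

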### Procedure

Participants will be recruited from the medical oncology, radiation oncology and haematology outpatient clinics from three major cancer centres in NSW, Australia. Initially, a research nurse will review clinic lists to identify patients who meet eligibility criterion (1). The list will then be reviewed by a clinician or clinic nurse to exclude patients who do not meet eligibility criteria (2), (3) and (4) and to make the initial approach to eligible patients. The research nurse will then provide a verbal and written explanation of the study to patients interested in the study and obtain their informed consent to participate. Consenting participants will be asked to nominate a caregiver and if the caregiver is present at the clinic at the time of recruitment, the research nurse will provide them with a verbal and written explanation of the study. If not, the caregiver information will be given to the patient who will be asked to pass it on to the caregiver. If the patient is unable to nominate a caregiver at the time of recruitment, s/he will be asked during the first and subsequent computer assisted telephone interviews (CATIs) to nominate a caregiver in case their circumstances change during the course of the study.

### Materials

Participants will complete bi-monthly CATIs over a period of 18 months. Primary outcomes include patient and caregiver unmet needs and patient service utilisation. Secondary outcomes include patient and caregiver anxiety, depression and quality of life and caregiver satisfaction with care.

#### Background questions

Socio-demographic questions will be asked including participant age, gender, marital status, level of education, type of health insurance, gross income and employment. Patients will also be asked about type of diagnosis and time since initial diagnosis; while caregivers will be asked about tasks performed in their care giving role as well as their relationship to and personal contact with the patient. A 12-item index [25] will assess co-morbid conditions, including cerebrovascular disease, inflammatory bowel disease, liver disease, gastric ulcers, arthritis, diabetes, depression, hypertension, chest pain, heart attack, heart failure, and chronic lung disease.

#### Primary outcomes

The 34-item Supportive Care Needs Survey - Short Form (SCNS-SF34) [17,26], plus six spirituality needs items and four additional needs items from the Needs Assessment for Advanced Cancer Patients (NA-ACP) [24]; will be used to assess the types and levels of unmet needs of patient participants. Patients will also be asked to report on their use of health care providers, support services and complementary and alternative medicines. For caregivers, the 44-item *Supportive Care Needs Survey -Partners and Caregivers *will be assessed (Girgis, Lambert & Lecathelinais: The Supportive Care Needs Survey for Partners and Caregivers of Cancer Survivors: Development and Psychometric Evaluation, submitted to *Psycho-Oncology*).

#### Secondary outcomes

Quality of life will be assessed using the two global questions from the European Organization for Research and Treatment of Cancer Quality of Life Questionnaire (EORTC QLQ-C30) instrument [27]; and anxiety and depression will be measured using the 14-item Hospital Anxiety and Depression Scale (HADS) [28]. A total HADS score will be obtained to quantify overall level of distress [29-31].

### Intervention

The intervention involves the systematic use of the NAT: PD-C to facilitate assessment and provision of needs-based care to address patient and caregiver physical and psychosocial concerns by health professionals involved in the care of people with advanced cancer. To support the uptake of the intervention, medical, nursing and allied health professionals at each of the recruitment sites will receive training in the use of the *Guidelines *and NAT: PD-C.

A systematic review of interventions to change provider behaviour found that guidelines were more effective if active educational interventions and patient-specific reminders were used to disseminate them [32]. The use of workshops and seminars were considered to assist in educating and training clinicians in the use of the *Guidelines *and NAT:PD-C, however research suggests that educational approaches using self-directed learning vary in effectiveness as health professionals vary in motivation to attend, change and self assess [33].

For this study, training in the intervention will be undertaken using an academic detailing approach, utilising individual as well as group sessions, as required. This approach involves a limited set of objectives delivered by expert trainers to individuals in their own environment at their own convenience to provide evidence based information regarding professional practices [34,35]. Group and individual academic detailing have both been shown to change health professional behaviours [36], particularly for those who received individual visits [37]. Academic detailing sessions are often more time efficient than workshops and seminars as they are brief, focused and delivered in the health professionals' own environment [38]; and health professionals have expressed a preference for this method along with audit and feedback [38].

